### Trial design {8}

The study hires a two-stage randomized controlled trial with 92 clusters with three arms for impact evaluation. In this study, we have two different forms of financial incentive schemes, CCT and LIS, combined with malaria education (EDU), consisting of two intervention arms, while the third arm is for control. We randomly assign these three arms at the cluster level at the first stage.

Clusters are defined as a set of 20 adjacent households based on the household location information obtained in the household census conducted in coastal communities of the Suba South Sub-County from May to July 2021 and include 5968 households. Although there are numerous ways to define 92 clusters with 20 adjacent households from 5968 households in the region, we randomly select a combination of 92 clusters in a way that none of the cluster-comprising households belong to more than one cluster.

Once we define the clusters, they are stratified by the average malaria prevalence and the number of children under 15 years of age in the clusters based on the baseline survey, and one of the three arms is assigned to each of the clusters per stratum based on random numbers generated by a priori on the computer. Figure 1 shows the locations of the clusters on the map and arm types by colors.

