### Sample size {14}

The malaria RDT positivity among residents in our target area is approximately 30%, based on an independent survey conducted at the same time in our study area. Our census survey suggested an approximate average household size of 5. We aim to detect the expected effect of 30% RDT positivity reduction (to 21%) relative to control both in the direct and spillover effects, with a power of 0.8, a two-sided type-I error of 5%, a cluster size of 20 households, and an intra-cluster correlation coefficient of 0.05. We rely on the optimal saturation [11] and find the required number of clusters is 28 for the control arm and 32 for the treatment arm, where ten households in a treatment cluster end up receiving the treatment, and the remaining ten households are left untreated. We have two intervention arms, each of which to compare to the control arm. Therefore, our total intervention sample consists of 9200 individual subjects from 1840 households grouped into 92 clusters.

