### Concealment mechanism {16b}

Each cluster is assigned the computer-generated quasi-random number generated in the way described above after the stratification of two baseline indicators: the number of children aged 0 to 15 and their malaria prevalence. The stratification creates four (2 × 2) strata. Then, clusters are arranged in ascending order of their assigned random numbers by stratum. In each stratum, seven clusters with the smallest random numbers are assigned to the control arm, 8 clusters with the next smallest numbers are assigned to the CCT arm, and 8 clusters with the largest random numbers are assigned to the LIS arm. There will be 28 control, 32 CCT, and 32 LIS clusters in total.

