## Data collection and management

### Plans for assessment and collection of outcomes {18a}

#### Baseline and follow-up surveys

Malaria prevalence will be estimated using cross-sectional malariometric surveys. These surveys will be conducted at baseline (before the intervention) and 6 months post-intervention. Malaria status will be determined using three methods: RDT, microscopy, and PCR. First, a finger prick blood sample will be collected for on-site diagnosis by Paracheck-Pf® RDT (Orchid Biomedical Systems, India). Survey participants with positive test results will receive a treatment course of artemether-lumefantrine with dosing instructions as per the guidelines from the Ministry of Health in Kenya. Blood smears will be prepared on-site and transported to the main laboratory in Homa Bay, where thin smears are fixed with methanol. All smears are stained with 3% Giemsa solution for 30 min and then examined by experienced microscopists. Two blood samples (70 µl each) will be collected with a 75-mm EDTA-coated micro-hematocrit capillary tube (Marienfeld, Lauda-Königshofen, Germany) and spotted on Whatman ET31 Chr filter paper (Whatman International. Maidstone, UK). The blood spots will be allowed to dry at ambient temperature and stored in individual zipped plastic bags at − 20℃. The dried blood spots (DBS) will be used for DNA extraction and determination of malaria status by PCR [14].

Malaria incidence will be assessed at the baseline and follow-up after 6 months post-intervention. CHVs will visit the households of the participants. A structured questionnaire created using the CSPro application and loaded on an Android-based tablet computer will be used to collect any history of fever, malaria episode, or visit to the local health facilities in the previous 3 months [15].

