## Statistical methods

### Statistical methods for primary and secondary outcomes {20a}

The intention-to-treat (ITT) analysis is the primary analysis approach for both the primary and secondary outcomes and the per-protocol analysis will be included as a supplementary analysis.

The primary outcome of the study is malaria prevalence by PCR of children aged 0 to 15 6 months after the financial incentive intervention. Based on the PCR examination results, we apply a regression model for two-stage randomized control trial settings, proposed by a study [11], which allows us to identify an unbiased estimate of the ITT and also the spillover effects on treated and untreated households within a cluster while controlling for confounders, including age, gender, house structure, and other socioeconomic status indicators.

For secondary outcomes, the PCR malaria prevalence of all the age groups, the microscopic malaria prevalence, the proportion of participants using the bed net, and the malaria knowledge of the adult participants will be evaluated similarly.

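### The covariates named for the primary regression do not name the randomisation strata or baseline malaria prevalence; adding both costs almost nothing and can shorten the confidence interval

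*Protocol article*

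**What the plan says.** Statistical methods {20a} takes the primary model from a cited paper on two-stage randomised designs and applies it "while controlling for confounders, including age, gender, house structure, and other socioeconomic status indicators". Secondary outcomes are to be evaluated similarly. The link function is not stated.

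Concealment mechanism {16b} says that each cluster received its random number "after the stratification of two baseline indicators: the number of children aged 0 to 15 and their malaria prevalence", and that "The stratification creates four (2 × 2) strata". Each stratum holds 7 control, 8 CCT and 8 LIS clusters. Trial design {8} describes the same step: clusters, "they are stratified by the average malaria prevalence and the number of children under 15 years of age in the clusters", use baseline survey data.

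Under Baseline and follow-up surveys, "Malaria status will be determined using three methods: RDT, microscopy, and PCR", and "These surveys will be conducted at baseline (before the intervention) and 6 months post-intervention". The trial therefore holds both the strata and a baseline value of the primary outcome for those who consented to sampling.

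**The concern.** Baseline prevalence mattered enough to the investigators to stratify on it, yet the analysis text names other covariates and not this one. Two separate things follow if the named covariates are the whole model.

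- **Strata.** Stratified allocation already reduces the true variability of the arm contrast. A model without the strata does not credit this reduction, so its standard error overstates the real uncertainty and the nominal 5% test rejects too seldom.
- **Continuous baseline prevalence.** A cluster's earlier malaria level may predict its later level better than a two-way split does. Including it can lower the true variability itself.

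Between-cluster variation is the larger part of the variance here (see the working), and these are cluster-level predictors. What is at stake is precision and the true size of the test. Bias is not at stake.

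**Working it through.** **Inputs from Sample size {14}.** Control positivity 0.30 ("The malaria RDT positivity among residents in our target area is approximately 30" per cent), reduced to 0.21; ICC 0.05; 28 control and 32 clusters per intervention arm; 20 households of about 5 people, half of them treated; power 0.80; two-sided 5%.

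**Assumptions.** About 50 children per cluster (half of 100 residents), hence about 25 in treated households. The correlation r between a cluster's underlying malaria level at baseline and at follow-up is not in the documents and is varied from 0 to 0.8.

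**The plan's own figure.** For treated households against control:

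Var = p0q0[ICC + (1-ICC)/n_c]/28 + p1q1[ICC + (1-ICC)/n_t]/32

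- With n_c = 100 and n_t = 50, SE = 0.0284 and power = 0.89.
- With n_c = 50 and n_t = 25, Var = 0.21(0.05 + 0.019)/28 + 0.1659(0.05 + 0.038)/32 = 0.000518 + 0.000456 = 0.000974. SE is then 0.0312 and power = Phi(0.09/0.0312 - 1.96) = 0.82.

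The stated 0.80 is not matched exactly from the stated inputs, which is a separate matter. In the second case the between-cluster part is 0.21 × 0.05/28 + 0.1659 × 0.05/32 = 0.000634, or 65% of the variance.

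**Simulation.** 92 clusters, four strata of 7/8/8, 3000 runs, cluster-level linear regression, ICC 0.05. Three models were compared: arms only (A); arms and strata (B); arms, strata and baseline cluster prevalence (C). True SD is the spread of the estimate over runs.

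| r | True SD, A | Reported SE: A | B | C | SE change, A to C | Type I error: A | B | C | Power: A | C |
|---|---|---|---|---|---|---|---|---|---|---|
| 0 | 0.0330 | 0.0339 | 0.0339 | 0.0341 | +1% | 0.039 | 0.040 | 0.040 | 0.75 | 0.74 |
| 0.3 | 0.0329 | 0.0340 | 0.0336 | 0.0335 | -1% | 0.041 | 0.045 | 0.045 | 0.75 | 0.76 |
| 0.5 | 0.0324 | 0.0339 | 0.0327 | 0.0322 | -5% | 0.041 | 0.047 | 0.047 | 0.76 | 0.81 |
| 0.7 | 0.0307 | 0.0340 | 0.0316 | 0.0303 | -11% | 0.026 | 0.040 | 0.039 | 0.76 | 0.85 |
| 0.8 | 0.0301 | 0.0340 | 0.0308 | 0.0289 | -15% | 0.027 | 0.043 | 0.046 | 0.77 | 0.88 |

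Four remarks on reading it:

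1. Strata leave the estimate unchanged, because every stratum has the same 7/8/8 split. Models A and B share one true SD, and only the reported SE moves.
2. Part of A's conservatism is not due to strata. The regression pools residual variance over arms with unequal numbers of children. At r = 0 the null contrast has variance 0.21 × 0.088/32 + 0.21 × 0.069/28 = 0.001095 (SD 0.0331). The pooled form is 0.21 × [(64 × 0.088 + 28 × 0.069)/92] × (1/32 + 1/28) = 0.001156 (SE 0.0340). The type I error to compare with is therefore about 0.04, against 0.026 and 0.027 in A at r = 0.7 and 0.8. Simulation error on such a rate is about sqrt(0.05 × 0.95/3000) = 0.004.
3. Absolute power depends on how variance under the alternative is modelled, so only the change should be read.
4. At an assumed ICC of 0.20, SE falls by 3%, 10%, 22% and 31% for r = 0.3, 0.5, 0.7 and 0.8. Type I error in A reaches 0.014 at r = 0.8.

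**Hand check of the gain.** Prevalence observed in 50 children measures the underlying level with reliability 0.05/(0.05 + 0.95/50) = 0.725. The between-cluster share of the pooled variance is 0.05/[(64 × 0.088 + 28 × 0.069)/92] = 0.05/0.0822 = 0.61. At r = 0.7 the expected variance reduction is 0.49 × 0.725 × 0.61 = 0.22. The simulation gives 1 - (0.0303/0.0340)² = 0.21.

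**The case against.** The strongest reply is that nothing has been omitted. The word *including* opens an illustrative list of confounders, strata are design factors rather than confounders, and an unseen analysis plan or the cited model may already contain them. It stands that the text does not exclude these terms, so a reader who infers that the plan has decided against them goes too far. It remains true that the section chose to name covariates and did not name the two with the clearest design rationale.

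The size is also open to challenge, and most of that challenge stands:

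- No value of r is given. At r = 0 nothing is gained, and at r = 0.3 very little.
- A reader might scale the whole between-cluster variance by (1 - r²), which gives variance reductions of 16%, 32% and 42% at r = 0.5, 0.7 and 0.8. That treats baseline prevalence as error-free and ignores the stratified allocation. The simulated reductions are about 10%, 21% and 28%.
- House structure and socioeconomic status may absorb part of the between-cluster variance. The simulation contains no such covariates.
- A reader might take the area with 68% positivity in the Background as proof of a strong correlation. Those data are dated December 2022 to February 2023, the follow-up window, and one time point cannot show persistence. Participants positive by RDT are also treated at the survey.
- Stratification already limits imbalance in baseline prevalence between arms; only residual imbalance within strata remains.

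**Conclusion.** The point holds as a recommendation on efficiency. The primary model as worded does not name the strata or baseline malaria, which the trial has. With the named covariates alone, its standard error would be too large and its test conservative if r is above zero. At the stated ICC the change in SE from adding both terms runs from about +1% (r = 0) to about -15% (r = 0.8). This rests on an assumed r, about 50 children per cluster, and a linear cluster-level model without the other covariates.

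Stronger readings are not supported. A reader might infer that the primary estimate would be biased or the trial invalid: the point estimate is unaffected, and the test errs on the cautious side. A reader might infer that the trial is underpowered for this reason: the sample size does not rely on covariate adjustment, and unadjusted power by the formula is 0.82 with 50 children per cluster. It should not be treated as a condition for validity.

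**What to change.** In {20a}, state that the primary model includes fixed effects for the four randomisation strata and the continuous baseline cluster PCR prevalence in children. The child's own baseline PCR status may be added where available; it will not exist for every child, because sampling required consent. State that all other covariates are taken at baseline, and name the test behind the prevalence used for stratification. Apply the same rule to secondary outcomes that have a baseline measurement; the article does not show that the knowledge quiz was given at baseline.

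If a logistic link is used, adjustment changes what the coefficient estimates, so state the estimand or report a marginal risk difference.

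The cost is one or two sentences and four degrees of freedom out of 92 clusters, at most about 1% in SE when r = 0. The strata and the baseline malaria tests for the primary outcome are already in hand. Follow-up is complete according to Trial status, so the wording should be fixed, and dated, before outcomes are compared by arm.

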### Interim analyses {21b}

Since no interim analysis or stopping guidelines have been planned. From the aspect of the benefit of the population, a stepped wedge design will be followed after this trial in the case that we confirm the net positive benefits of the intervention.

### Methods for additional analyses (e.g., subgroup analyses) {20b}

As malaria infection risk differs depending on socioeconomic status [16], we are also interested in whether the intervention effects could differ across socioeconomic status. Using socioeconomic variables collected in the baseline survey, such as the wealth index of households and education level of household heads, we will do subgroup analyses. For the additional analyses, we also use the regression model for two-stage randomized experiments [11].

### Methods in analysis to handle protocol non-adherence and any statistical methods to handle missing data {20c}

The extent and patterns of missing data will be assessed once all data collection has been completed. If necessary, multiple imputation methods will be used to handle missing data.

### Plans to give access to the full protocol, participant-level data, and statistical code {31c}

This manuscript is the full protocol. The corresponding author will make the de-identified datasets or any future statistical code available upon reasonable request.

## Oversight and monitoring

### Composition of the coordinating center and trial steering committee {5d}

The sampling team, composed of CHVs and laboratory technicians, set up a day-to-day communication group and exchanged their experiences. A local management team of study investigators from Kenya and Japan also joined this, leading and advising the activities and monitoring the sample and data integrity. A monthly meeting will be held by the steering committee composed of all key researchers from Kenya and Japan, including the principal investigator (PI) and co-PI, which aim to monitor the progress of the trial.

### Composition of the data monitoring committee, its role and reporting structure {21a}

Because this intervention is considered to be of a low-risk nature, this study does not have a data monitoring committee. For additional credibility regarding study quality, the researchers will consult a third statistician if necessary.

### Adverse event reporting and harms {22}

Neither the financial incentive nor the malaria education is known to pose significant health or safety risks. Nonetheless, all unanticipated problems will be reported to the research team and Homa Bay County Ministry of Health (MOH) through CHVs. Medical officers from Homa Bay County will assess the relatedness of the reported events to the study and report to the research team, including the PI. In the event of a study-related serious adverse event, the study team will convene a meeting immediately with the MOH and Homa Bay County Teaching and Referral Hospital representatives to review the case and take necessary action.

### Frequency and plans for auditing trial conduct {23}

After participant recruitment, enrollment, and implementation of the intervention are completed, the research team will have a meeting to review the protocols for outcome evaluation. A monthly meeting will be held during the follow-up period to ensure that all surveys and investigations are conducted according to the study protocol. The study is required to submit annual reports and renewal to ethical review boards of Otaru University of Commerce, Japan, and Mount Kenya University, Kenya.

### Plans for communicating important protocol amendments to relevant parties (e.g., trial participants, ethical committees) {25}

Decisions on important trial amendments must be made through a formal procedure and will be approved by institutional review boards (IRB) at Mount Kenya University and Otaru University of Commerce. The protocol in the clinical trials registry will also be updated accordingly.

### Dissemination plans {31a}

The results will be shared with the Homa Bay County Government and Kenya National Malaria Control Program and discussed for the possibility of expanding the program. Also, the results will be disseminated through publications and conferences to help the development of novel malaria control strategies in other malaria-endemic countries. The feedback from the research participants will also help shape the future improvement of the intervention and acceptance by the communities.

## Discussion

Since around 2000, the United Nations/Millennium Development Goals (MDGs) and the establishment of the Global Fund have increased funding for global malaria control, and there have been significant improvements in the supply side of healthcare services for malaria control, including the distribution of long-lasting insecticidal nets (LLINs), implementation of indoor residual spraying (IRS), rapid diagnostic test (RDT), and artemisinin-based combination therapy (ACT) in community health facilities. In fact, the number of malaria cases and deaths worldwide has decreased significantly to the point where malaria elimination by 2030 was targeted as one goal in the 2015 United Nations Sustainable Development Goals (SDGs). However, while there has been a marked contraction of malaria prevalence in Southeast Asian countries, tropical Africa continues to experience high malaria prevalence. Indeed, Suba South Sub-county, Homabay County, Kenya, located in the Lake Victoria basin, has shown high malaria prevalence despite the intensive malaria control efforts by national and international aid agencies. One possible major cause of this residual transmission is the low motivation of the residents for malaria prevention and early treatment. For example, in the target areas, residents have been observed using mosquito nets distributed free of charge for purposes other than malaria control.

In this study, we aim to develop a policy tool that alters residents’ attitudes and behaviors for malaria elimination. Our proposed plan is a financial incentive intervention for residents in malaria-prone areas complemented with malaria education. The intervention includes two components. The first component is the introduction of a financial incentive scheme tied to negative RDT results for malaria infection among the target population. This is an attempt to promote behavioral changes in the population by providing monetary incentives. The project has two different forms of incentive schemes. One is a conditional cash transfer (CCT) that offers a small reward (200 Ksh) for non-infected subjects during the follow-up survey, and the other is a lottery incentive scheme (LIS) that gives a lottery with a 10% chance of winning a large reward (2000 Ksh) instead of the small reward. The CCT is an incentive scheme widely used in educational or medical aid interventions to promote behavioral changes in a target population. On the other hand, The LIS is a relatively new scheme with few applications and a variant of the CCT that uses findings from the behavioral sciences. Specifically, the LIS scheme utilizes the finding on subjective probability in behavioral science that people tend to overestimate the probability of events with a small probability of occurrence [17–19]. Suppose such a tendency exists among many people. In that case, the LIS may incentivize people more than the CCT. Moreover, if the LIS works as an incentive scheme, it also has a practical advantage against the CCT. Since the reward is paid with probability to a pool of candidates who meet the payment conditions in the LIS, the number of people receiving rewards is much less in the LIS than in the CCT, thus reducing the operational cost [20].

The second component is malaria education using animated tablet-based malaria educational material (EDU) developed by the research team. It complements the incentive scheme by providing the appropriate knowledge to the residents for malaria elimination. The educational content includes the medical knowledge necessary for malaria control, such as disease characteristics, transmission mechanisms, and prevention methods. Also, it explains asymptomatic and sub-microscopic malaria infection, its high prevalence in the region, and the risk of transmission from asymptomatic infected individuals, which have recently attracted attention as obstacles to malaria control among experts, although the local population does not know [21].

Furthermore, it includes the economic losses caused by malaria disease and the benefits of prevention and early treatment. The content introduces the direct and indirect costs of treatment for malaria disease, lost income due to absence from work, the decline in children’s academic performance caused by school absence, and the possibility of loss of future opportunities, based on the findings from the existing economics literature.

It is worth discussing the rationale for providing financial incentives to residents for malaria prevention. Firstly, in infectious diseases such as malaria, individuals’ actions for prevention and early treatment benefit their neighbors because such actions lower the infection risk of the neighbors. People often do not consider such spillover effects when they decide their effort level for malaria control. Thus, voluntary efforts of individuals to prevent infection tend to be lower than the socially optimal level [8–10]. Financial incentives may enhance individuals’ efforts for malaria prevention toward the socially optimal level.

Secondly, currently, massive private and public resources have been used for malaria control and treatment. The financial incentives may be able to save such resources for malaria control by lowering malaria risks in the region. According to our census data in 2021 in the region, for example, 17.2% of working adults (above 15 years old) had at least one malaria episode during the last 12 months, where we counted only cases diagnosed by malaria tests, spent 120 Ksh for transport to health facility and 480 Ksh for treatment on average, and took 7.7 days for the recovery. Working adults get 260 Ksh daily and work 5 days a week on average. A simple calculation tells us that one malaria episode of a working adult costs 2030 Ksh (120 for transport, 480 for treatment, and 1430 for foregone earnings) on average. If the cost of the public resource for their treatment is counted and also if the cost of family members and neighbors who get malaria infection from them is counted, the total cost of one malaria episode will be much more than our calculation. Thus, we believe that social gain from reducing malaria risk could be significant, and hence, it is valuable to consider a policy tool such as the financial incentive intervention to alter the residents’ behaviors for malaria prevention.

The cost calculation also gives us a rough idea of at which level to set the reward in our financial incentive intervention. Our intervention set the reward amount at 200 Shillings for the CCT and 2000 Shillings with a winning probability of 10% for the LIS. The expected amount of reward is the same between the schemes for comparison purposes and also similar to the expected cost that an individual adult has to incur for malaria treatment for a period of 6 months (which is the duration from the intervention to the follow-up survey). As mentioned earlier, on average, the cost of one malaria episode in an adult was 2030 Shillings. The average number of malaria infections per adult would be 0.094 for 6 months, given the probability of having at least one malaria episode for 12 months (17.2%) under the assumption of the Poisson process on the number of individual malaria infections. This simple calculation gives us the expected private cost of approximately 190 Shillings for malaria treatment for 6 months.

This study has several limitations. First, the financial incentive schemes are designed so that the monetary rewards are tied to the negativity of RDT in the follow-up rather than that of the PCR despite the low sensitivity of RDT, especially for low parasitemia cases. This is due to a practical reason. It takes only 15 min to obtain the RDT results, and hence, both participants and survey teams can observe the RDT results together and the reward status for the eligible household members on the spot. On the other hand, the PCR results are obtained only in a well-equipped laboratory and need several days, including the transportation and sorting of blood samples. The verifiability of the reward condition on the spot is important for the participants to trust in the incentive scheme since if the participants do not trust it, they will not respond to it. However, we should cautiously consider that the rewards would be given to those with asymptomatic and sub-microscopic infection if the RDT fails to detect such infection, which happens more often than the PCR. Ideally, we should not give rewards for such cases since sub-microscopic infection is the one we also want the participants to avoid. We will continue monitoring the participants’ behaviors after the follow-up survey.

Second, there are some neighboring clusters with almost a negligible buffer, and hence, there is a possibility of inter-cluster influence due to the close proximity of physical and social distance between participants in neighboring clusters. This possibility may violate the stable unit treatment value assumption (SUTVA). Thus, we may need to consider a method to estimate the treatment effect under the possibility of the violation of the SUTVA by following a recent study [22].

Third, the household-level randomization for the treatment assignment will be done by asking the household representative to draw a card with a sealed number during the household visit in the intervention clusters, and the treatment status will be determined by the number on the card and known by the participants. This may cause non-random attrition in the follow-up survey due to the reluctance of those who fail to get the treatment to participate in the follow-up survey. We may need to handle the sample attrition carefully because it can be associated with the treatment status within the intervention clusters.

This study will be the first trial to evaluate the financial incentive schemes on the infection incidence by active case detection and the malaria preventive behaviors of the residents in a malaria-prone area. Results from this study will inform decision-makers who seek an effective policy tool for malaria elimination.

